## Abstract

**Background:**

Sleep deprivation is common in critically ill patients in intensive care units (ICU). It can result in delirium, difficulty weaning, repeated nosocomial infections, prolonged ICU length of stay and increased ICU mortality. Melatonin, a physiological sleep regulator, is well known to benefit sleep quality in certain people, but evidence for the effectiveness in ICU sleep disturbance is limited.

**Methods/Design:**

This study has a prospective, randomized, double-blind, controlled, parallel-group design. Eligible patients are randomly assigned to one of the two treatment study groups, labelled the ‘melatonin group’ or the ‘placebo group’. A dose of 3 mg of oral melatonin or placebo is administered at 9:00 pm on four consecutive days. Earplugs and eye masks are made available to every participant. We plan to enrol 198 patients. The primary outcome is the objective sleep quality measured by the 24-hour polysomnography. The secondary outcomes are the subjective sleep quality assessed by the Richards Campbell Sleep Questionnaire, the anxiety level evaluated by the Visual Analogue Scale-Anxiety, the number of delirium-free days in 8 and 28 days, the number of ventilation-free days in 28 days, the number of antibiotic-free days, ICU length of stay, the overall ICU mortality in 28 days and the incidence and severity of the side effects of melatonin in ICU patients. Additionally, the body stress levels, oxidative stress levels and inflammation levels are obtained via measuring the plasma melatonin, cortisone, norepinephrine, malonaldehyde(MDA), superoxide dismutase(SOD), interleukin-6 (IL-6) and interleukin-8 (IL-8)concentrations.

**Discussion:**

The proposed study will be the first randomized controlled study to use the polysomnography, which is the gold standard of assessing sleep quality, to evaluate the effect of melatonin on the sleep quality and circadian rhythms of ICU patients. The results may recommend a new treatment for ICU patients with sleep deprivation that is safe, effective and easily implementable in daily practice.

**Trial registration:**

This study was registered with ClinicalTrials (NCT; registration number: ChiCTR-TRC-14004319) on 4 March 2013.

## Background

Sleep deprivation is a major concern in critically ill patients in intensive care units (ICU). Several studies have shown that poor sleep quality and the inability to sleep are the second largest stressors and rank among the top three major sources of anxiety during ICU stays
[1–3]. Sleep for ICU patients is characterised by frequent disruptions, loss of circadian rhythms and a paucity of time spent in restorative sleep stages. Typical findings described by polysomnography (PSG), the gold standard of assessing sleep quality, include increased latency, a higher proportion of non-rapid eye movement (NREM) sleep stage 1 and 2 (or light sleep), and reduced restorative slow wave (SW) and rapid eye movement (REM) sleep, largely because of frequent waking. Although ICU patients may experience normal or near normal total sleep time (TST), approximately 50% of this sleep occurs during the daytime
[4, 5]. In a recent observational study by Elliot *et al.* a 24-hour PSG was used to evaluate the sleep quality in ICU patients
[5]. They found that despite improvements in ICU design, technology and healthcare personnel training, there has been no improvement in the ICU sleep problem
[5–7]. It has been found that there are many extrinsic and intrinsic factors of sleep deprivation in the ICU setting including noise, light, nursing procedures, the presence of existing diseases, inflammatory mediators, anxiety, pain, sedative and opioid medications and mechanical ventilator setting
[8–12]. Furthermore, the occurrence of ICU sleep deprivation is associated with detrimental outcomes, including delirium, difficulty weaning, increased nosocomial infections, prolonged ICU length of stay (LOS) and increased ICU mortality
[13].

Conversely, despite the poor sleep quality that disturbs almost all ICU patients, clinicians remain reluctant to administer traditional sedative-hypnotic drugs in patients with sleep disorders. The major concerns are the side effects of these drugs, mainly that they destroy the structure of sleep, reduce the clinician’s ability to monitor the level of consciousness, induce respiratory depression and lower blood pressure
[14].

Sleep goals for ICU patients are to get enough sleep, reset the disordered circadian rhythms, adjust the abnormal sleep structure, reduce sleep interruption, overcome fatigue and anxiety, facilitate nursing care and treat disease. An ideal therapy for improving sleep in the ICU should be economical, feasible, rapid in onset and offset and without local and systemic adverse effects. At present, there is no effective treatment in use to improve ICU sleep that covers all of these ideal properties. Current studies are mainly focused on non-drug treatments such as earplugs and/or eye masks
[10, 15] and imagery and relaxation
[16]
*.* These treatments are relatively safe but do not guarantee efficacy. Among the studies, the clinical research on earplugs and/or eye masks has some maturity
[15]. Some domestic and international experts and scholars have recommended that ICUs incorporate earplugs and/or eye masks into routine nursing care
[17]. However, Bourne *et al*.
[18] and Gabor *et al*.
[7] showed that environmental factors were responsible for a fraction of arousals and awakenings, and Perras *et al*.
[19] indicated that the physiological regulation of melatonin secretion by darkness and light was abolished in severely ill patients in the ICU. Therefore, treatments based on environmental factors might have limited effects. Recently melatonin, a physiological sleep aid, has gained interest among ICU scholars.

Melatonin (N-acetyl-methoxytryptamine) is a neurohormone mainly secreted by the pineal gland. Light signals play the most important role in the synthesis and secretion of melatonin in organisms. Thus, the environmental cues that regulate an organism’s biological clock are predominantly the daily alternation of light and darkness acting via the retina and retina-hypothalamic pathways directly on the suprachiasmatic nuclei (SCN). Melatonin secretion increases directly with the length of darkness. Increased light intensity decreases the quantity of endogenous melatonin produced and shifts the pattern of release throughout the circadian clock. Endogenous melatonin is released at night, beginning at approximately 9:00 pm with a peak release at between 2:00 and 4:00. Melatonin release is typically inhibited between 7:00 and 9:00, coinciding with the peak of endogenous cortisol
[20]. This secretion pattern makes the physiological activities in the human body, such as the sleep-wake cycle, synchronised with the circadian rhythm. Thus, melatonin is a good sleep aid. In addition, current *in vitro* and *in vivo* experiments suggest that melatonin might act as a mood stabilizer, relieve stress, act as an anti-oxidation and anti-inflammation agent, suppress pathogens and protect the functioning of multiple organs
[20], which are undoubtedly helpful to the recovery of ICU patients, and thereby might improve sleep.

Prolonged-release melatonin (Circadin), an oral medication to regulate physiological sleep and the circadian rhythm designed to mimic the endogenous pattern of melatonin production, is licensed for the treatment of primary insomnia in patients aged 55 years and over. It results in significant and clinically meaningful improvements in sleep quality, morning alertness, sleep onset latency and quality of life, without withdrawal symptoms upon discontinuation
[21]. Recently, extensive clinical trials also noted that melatonin could be beneficial in different populations with sleep disorders. Firstly, melatonin might be effective for insomnia and daytime sleepiness caused by time zone changes
[22] and work shifts
[23] that induce the malfunctioning of biological clocks. This is because melatonin may maintain the synchronisation in situations where the circadian rhythms are jeopardized and resynchronize after a period of free-run release. Secondly, melatonin might improve the sleep quality of non-ICU critically ill patients with dialysis
[24], moderate to severe COPD
[25] and asthma
[26]. In addition, the available clinical data shows that perioperative use of melatonin is effective in reducing preoperative anxiety
[27] and plays a role in the prevention of postoperative delirium
[28], as well as possessing certain analgesic qualities, and may reduce concomitant opioid use in the postoperative period with a corresponding reduction in opioid-associated side effects
[29].

Melatonin has been given safely to humans in doses of 1 to 15 mg. Although treatment results in plasma levels up to 100 times the normal peak night concentration approximately 1 hour after ingestion, it has a wide safety margin
[30]. In a meta-analysis, Buscemi *et al*. concluded that melatonin is safe for short-term use
[31]. They found that the most common side effects of melatonin use were headache, dizziness, nausea and drowsiness
[31]. Most importantly, although melatonin has hypnotic, sedative and analgesic properties, it has few respiratory and hemodynamic effects.

The interest in melatonin as a potential therapeutic or prophylactic agent in the management of sleep disturbance in the ICU derives from the demonstrated low plasma concentrations and altered secretion patterns of melatonin in critically ill patients. Shilo *et al*. studied the day secretions of melatonin in a group of ICU patients compared to a group of patients in ordinary medical wards. They found that the nocturnal peak of melatonin was missing in most ICU patients
[32]. Mundigler *et al*. described a disturbed pattern of circadian secretion of melatonin in ICU patients with sepsis (16 out of 17 patients) but a preserved circadian rhythm in ICU patients who did not have sepsis (six out of seven patients)
[33]. Olofsson *et al*. found that the circadian rhythm of melatonin secretion was abolished in mechanically ventilated patients in the ICU
[34]. Perras *et al*. suggested that the nocturnal melatonin concentrations in ICU patients were negatively correlated with illness severity
[19]. In addition, various drugs commonly used in the ICU have been reported to alter melatonin secretion and to decrease the plasma levels of melatonin
[35] including benzodiazepines, non-steroidal anti-inflammatory drugs (NSAIDs), corticosteroids and beta-blockers. Therefore, low melatonin levels, poor sleep quality and illness have a reciprocal causation interaction and form a vicious circle. The supplementation of exogenous melatonin to remodel the melatonin level in the human body that approaches the physiological state might be one of most effective strategies for improving sleep.

Both melatonin and cortisol are biological markers of the circadian rhythm. Some previous studies have shown that there is a hypo-secretion of melatonin and an overall high cortisol excretion in most patients in the ICU. Cortisol is an important stress hormone that would be invoked by the noise, light and other stressors in the ICU and leads to anxiety and sleep disturbance. It is known that melatonin can reduce the adrenocortical response to stress and down-regulate the synthesis and release of cortisol. Moreover, in addition to reducing the stress, the role of melatonin as an antioxidant and anti-inflammatory agent or part of sepsis treatment is widely discussed. Thus, administration of melatonin might significantly benefit ICU patients.

Recently, Mistraletti *et al*. studied the pharmacokinetics of melatonin given orally to ICU patients and found a good oral bioavailability of the drug
[36]. Additionally, several studies suggest it can take up to three days to achieve the desired effect of melatonin on sleep quality
[13, 18, 30, 37]. Until now, there have been only three studies investigating the influence of melatonin treatment on sleep quality in critically ill patients. Shilo *et al*.
[37] and Bourne *et al*.
[18] found that melatonin improved sleep quality and sleep length in critically ill patients in the ICU, however Ibrahim *et al*.
[30] found a negative result in their study. There are some inconsistencies regarding the inclusion criteria, the drug included, the sound and light control and the monitoring method in these three studies, specifically as follows:(1) Ibrahim *et al*.’s study included patients who had unlimited use of sedatives and analgesics that might affect serum melatonin levels; (2) there was no uniformity for the control of patient exposure to noise and light among the three studies, which may have a more powerful effect on observed sleep than even the pharmacological levels of melatonin achieved; and, most significantly, (3) they did not use the PSG (the gold standard for assessing sleep) to evaluate sleep quality and ignored the importance of monitoring the all-day sleep, likely because it is very difficult to perform 24-hour PSG in severely ill patients in the ICU.

The aim of the present work is to evaluate the efficacy and safety of melatonin for ICU sleep deprivation. Our hypothesis is that melatonin will improve the sleep quality in ICU patients. The present article proposes a protocol for a clinical study consisting of a double-blind, randomized, placebo-controlled trial with melatonin in adult critically ill patients with ICU sleep deprivation. The present report will follow the guidelines expressed by the Consolidated Standards of Reporting Trials (CONSORT).

## Methods/Design

### Study design and outcomes

The present study is a prospective, single-centre, randomized, double-blind, placebo-controlled, two-arm trial in patients with sleep deprivation in the ICU. All eligible patients in the ICU will be 1:1 randomized to the treatment intervention with melatonin or placebo. The objective of the trial is to evaluate the efficacy and safety of melatonin for ICU sleep deprivation. The definitions of the variables in the objectives are reported in Table 
1.

**Table 1 Tab1:** **Definition of study objectives**

Objective	Definition
Objective sleep quality	Total sleep time, the length of sleep at night (9:00 pm - 7:00 am) and during the day (7:00 am - 9:00 pm), sleep architecture (NREM stage 1 and 2, SWS, REM), and sleep disruption (the number of arousals and duration of sleep), which will be monitored for one 24-hour period using a portable PSG device.
Subjective sleep quality	The subjective feelings of nightly sleep status of the patient, including sleep depth, wake time after sleep onset, number of awakenings after sleep onset, latency to sleep onset, and sleep quality. It will be evaluated using the RCSQ [38, 39].
Anxiety level	ICU anxiety is defined as a state marked by apprehension, agitation, increased motor activity, number of arousals, and fearful withdrawal during the ICU stay [40]. It will be assessed using the VAS-A.
Delirium-free days in 8 and 28 days	Number of days that the patient is not delirious over 8 and 28 days starting from the day of inclusion. Patients are diagnosed as delirious when they have at least one positive CAM-ICU screening during their ICU stay. A delirium-free day is defined as a negative CAM-ICU screening during that day. In case a delirious patient is discharged from the ICU, a delirium-free day is defined as a delirium observation scale score of less than 3 during a complete day [41].
Ventilator-free days in 28 days	Time in days that the patient is not on a mechanical ventilator. If the patient is ventilated mechanically, including invasive and non-invasive ventilation several times during one ICU admission, then the non-ventilator times are added. Ventilator-free days (in 28 days) will be calculated.
Antibiotic-free days in 8 and 28 days	Number of days that the patient does not require any antibiotics at 8 and 28 days from randomization will be calculated.
ICU length of stay	Duration of admission to the ICU.
Overall ICU mortality at 28 days	Survival time will be assessed. Patients will be classified as either alive at study day 28 or dead at study day 28. Differences between the two strategies in mortality rates will be evaluated using the assumption of asymptotic normality. Estimates of relative risks and odds ratios and the corresponding 95% confidence intervals will be presented.
Side effects	Headache, dizziness, nausea, and drowsiness, determined daily by physical examination by the intensivist, and withdrawal symptoms upon discontinuation evaluated after the drugs are stopped.

NREM, None rapid eye movement; SWS, Slow wave sleep; REM, Rapid eye movement; PSG, Polysomnography; RCSQ, Richards Campbell sleep questionnaire; VAS-A, Visual analogue scale-anxiety; CAM-ICU, The confusion assessment method for the intensive care unit.

The primary outcome will be to determine the effect of melatonin administration on the 24-hour sleep-wake cycle and subjective sleep quality, including night/day sleep time, total sleep time(TST), percentages of NREM stage 1/2, slow wave sleep(SWS) and REM, the incidence of arousals per hour, the duration of sleep without waking and the number of sleep periods.

The secondary outcomes will be: (a) objective sleep quality as assessed by the Richards Campbell Sleep Questionnaire (RCSQ); (b) anxiety levels measured using the Visual Analogue Scale-Anxiety (VAS-A); (c) stress levels via measuring the plasma melatonin, cortisone and norepinephrine; (d) levels of oxidative stress; (e) levels of inflammation; (f) the number of delirium-free days in 8 and 28 days; (g) the number of ventilator-free days in 28 days; (h) the number of antibiotic-free days in 8 and 28 days; (i) ICU length of stay; (j) overall ICU mortality at 28 days; (k) the incidence and severity of melatonin side effects in ICU patients.

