The sound and illuminance levels are recorded from day 1 to day 6 using the integrated sound pressure level meter and the illuminance level meter. Continuous equivalent sound pressure levels (Leq) in ‘A’ weighted decibels and peak sound pressure levels (Lpeak) in ‘C’ weighted decibels are logged every second. The illuminance level (in lux) is recorded once per minute using a sensor placed close to the patient’s head. The bedside nurse should be asked to log an event whenever the patient received treatment or care. The event log will contain the following items: clinical assessment, tracheal suctioning, pressure area care, physiotherapy, mouth or eye care, blood test (sampling), washing, non-invasive blood pressure, eating and drinking, dressing, pain, line insertion and X-ray. Drug records are compiled daily for drugs that are known to adversely affect sleep or melatonin pharmacokinetics.

At the time of the ICU discharge, patients’ data and vital statuses, lengths of mechanical ventilation, the number of days of antibiotics use, the number of delirium-free days, the length of the ICU stay and ICU mortality will be recorded.

To investigate the enteral absorption and metabolism of orally administered melatonin in critically ill patients during their ICU stay and to evaluate the serum melatonin levels and their circadian variations in these patients, the melatonin levels are measured in blood samples taken on days 1 and 2 (before the intervention) and days 5 and 6 (four days after the intervention) at 20:45 (before administration), 9:10 pm, 9:30 pm, 00:00 am, 3:00 am, 6:00 am, 2:00 pm and 8:00 pm in 20 patients from each group. The plasma levels of norepinephrine and cortisol are also measured at the same time points. In addition, plasma levels of SOD, MDA, catalase (CAT), IL-6 and IL-8 are measured at 07:00 am on days 2 and 6.

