### Statistical analysis

All analyses will be performed according to the intention-to-treat principle, that is, all randomized patients will be analysed in the groups to which they were originally allocated and will be blinded to treatment assignment. Baseline patient characteristics will be compared and described using the appropriate statistics. Categorical variables will be presented as the numbers and percentages and will be analyzed by the *χ*^2^- tests or Fisher’s exact tests, or when appropriate, as relative risks. Continuous variables will be checked for normal distribution by the Kolmogorov-Smirnov test. Normally distributed variables will be expressed by their mean and standard deviation; non-normally distributed variables will be expressed by their medians and 95% confidence levels. Comparisons of continuous variables will be performed using Student’s *t*-test for normally distributed variables and the Mann-Whitney U test for non-normally distributed variables. Appropriate (linear, logistic, or Poisson) regression will be generated for the identification of the determinants of outcomes and for the correction of baseline covariates.

One-way repeated measures analysis of variance (ANOVA) were used to determine differences in the sleep variables, the subjective sleep quality, anxiety levels and plasma levels of melatonin, cortisol and norepinephrine. Twenty-eight day mortality will be analysed according to the Kaplan-Meier method and the results will be compared with the log-rank test hazard ratios and reported with 95% confidence limits. The number of delirium-free days, ventilation-free days and antibiotics-free days will be tested by Student’s *t*-test for normally distributed data and the Mann-Whitney U-test for non-normally distributed data. The differences in adverse events between the intervention and placebo groups are used for safety analyses. All tests of significance will be at the 5% significance level and two-sided. All of the data in this trial will be assessed with SPSS Statistics version 20.0 (SPSS, Chicago, Illinois, United States). The main analysis will be fully specified before unmasking.

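### Ventilator-free and antibiotic-free days carry no alive condition or value for deaths, and ICU stay is counted from admission, so these secondary outcomes can understate harm and lose precision

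*Protocol article*

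**What the plan says.** Table 1 of the protocol article (Definition of study objectives) gives the working definitions:

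- Antibiotic-free days: "Number of days that the patient does not require any antibiotics at 8 and 28 days from randomization will be calculated".
- Ventilator-free days: "Time in days that the patient is not on a mechanical ventilator". Separate spells off the ventilator within one ICU admission are added, and a 28-day figure is calculated. No start of the 28 days is stated.
- ICU length of stay: "Duration of admission to the ICU".
- By contrast, for delirium: "A delirium-free day is defined as a negative CAM-ICU screening during that day". That requires an observation on the day.

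Mortality is a separate secondary outcome ("overall ICU mortality at 28 days"), and Table 1 classifies each patient as alive or dead at day 28.

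Under Statistical analysis, "The number of delirium-free days, ventilation-free days and antibiotics-free days will be tested by" Student's t-test or, if non-normal, the Mann-Whitney U test. Death is not mentioned there for these counts.

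Trial interventions sets time zero at randomisation. Data collection and management lists, among the items recorded at ICU discharge, "the number of days of antibiotics use, the number of delirium-free days, the length of the ICU stay and ICU mortality". It also lists ICU length of stay before inclusion among the baseline items.

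**The concern.** A free-day count is meant to rise when a patient does better. With no alive condition, a patient who has died is neither ventilated nor on antibiotics, and so satisfies both definitions on every later day of the window. Subtracting recorded days of antibiotic use from 28 would produce exactly that score. An early death can then outrank a survivor who needed a longer course of treatment, in a t-test and in a Mann-Whitney test alike. ICU stay has the same weakness, because a stay cut short by death scores as a short stay.

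ICU stay has a second problem. Patients enter with a tracheotomy, at the weaning stage, and at least 36 hours after sedation was stopped, so part of the admission lies before randomisation. Treatment cannot change those days. Counting them adds variability to the outcome and makes a real difference harder to detect.

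**Working it through.** The protocol states no figure for these outcomes, so there is nothing to reproduce. The calculations below are illustrations. Mortality, time of death, survivor means and the spread of ICU stay are all assumptions.

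**1. Score of a single patient.** Assume ventilator and antibiotics continue until death on day d. Literal score = 28 - d, and for the 8-day antibiotic count max(0, 8 - d).

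| Death on day | Free days of 28, literal | Antibiotic-free days of 8, literal | Deaths scored 0 |
|---|---|---|---|
| 3 | 25 | 5 | 0 |
| 5 | 23 | 3 | 0 |
| 7 | 21 | 1 | 0 |
| 14 | 14 | 0 | 0 |

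A survivor treated for 10 days scores 28 - 10 = 18, below a patient who died on day 5.

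**2. Difference between arms.** Let p be mortality, m the mean free days among survivors (the same in both arms) and d the day of death. The arm mean is (1 - p) × m + p × v, with v = 28 - d literally or v = 0 if deaths score zero. For an excess mortality Δp in one arm, its difference from the other arm is:

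- literal: Δp × [(28 - d) - m]
- deaths scored 0: -Δp × m

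With Δp = 0.10:

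| Survivor mean m | Death on day d | Literal difference | Deaths scored 0 |
|---|---|---|---|
| 10 | 5 | 0.10 × (23 - 10) = +1.3 | -1.0 |
| 14 | 7 | 0.10 × (21 - 14) = +0.7 | -1.4 |
| 14 | 14 | 0.10 × (14 - 14) = 0.0 | -1.4 |
| 18 | 5 | 0.10 × (23 - 18) = +0.5 | -1.8 |
| 18 | 14 | 0.10 × (14 - 18) = -0.4 | -1.8 |

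Over m = 10 to 18 and d = 5 to 14, the literal difference runs from +1.3 to -0.4 days and the zero-scored difference from -1.0 to -1.8 days. The gap between the two scorings is Δp × (28 - d), that is 2.3 days for deaths on day 5 and 1.4 days for deaths on day 14. This gap measures how far the scoring rule moves the comparison. It is not the net advantage of the higher-mortality arm.

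**3. ICU length of stay.** Let k be the SD of pre-randomisation stay divided by the SD of post-randomisation stay, with the two parts independent. The SD of the whole stay is √(1 + k²) times the post-randomisation SD, so a standardised effect δ shrinks to δ/√(1 + k²). The planned 99 patients per arm (Current sample size justification) give 80% power for an assumed δ = 0.40 on post-randomisation stay (two-sided 5%).

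| k | Effective δ | Power, 99 per arm | n per arm for 80% power |
|---|---|---|---|
| 0 | 0.40 | 80% | 99 |
| 0.5 | 0.36 | 71% | 123 |
| 1 | 0.28 | 51% | 197 |
| 2 | 0.18 | 24% | 491 |

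Randomisation makes the expected pre-randomisation stay equal between arms, so the expected difference is unchanged. Only its precision suffers.

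**The case against.** The strongest reply is that the text is silent on death. A reader might infer that the plan credits days after death as free days; it nowhere says so, and a fuller protocol or analysis plan could add a rule. One can also argue that counting stops at ICU discharge or death: the ventilator row speaks of one ICU admission, End of participation in the study lists ICU discharge and death, and treatment days are recorded at discharge. A ventilated patient who died on day 5 would then score 0. The silence is a fair point and limits the claim to the literal wording. The second reading does not rescue the definition, because a survivor discharged early would lose the free days that followed discharge.

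A reader might also infer that the wording always favours the arm with more deaths, or by as much as 0.10 × 23 = 2.3 days. Neither follows. The 2.3 days leaves out the free days those patients would have had as survivors. With a survivor value of 18, the net is 0.10 × (23 - 18) = 0.5 days, and with later deaths the literal difference can be negative.

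A third tempting inference is that pre-randomisation stay biases the comparison. It does not: chance imbalance is ordinary sampling error. Pre-inclusion stay is recorded, and Statistical analysis allows correction for baseline covariates, though it does not commit to this for ICU stay. No power is claimed for ICU stay.

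It is also true that antibiotic-free days already start at randomisation, that mortality is reported separately, and that a rank test is planned for non-normal counts. None of these gives a deceased patient a sensible free-day score.

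**Conclusion.** The point holds in limited form. As worded, the ventilator-free and antibiotic-free definitions let an early death score well, and the planned tests use the counts directly. This goes beyond missing detail, because the same table settles finer matters, such as repeated ventilation spells and delirium after ICU discharge, and following its wording gives a worse measure. Under the assumed inputs harm is understated throughout, and in part of the range its sign reverses. The actual size depends on mortality and timing of death, which the protocol does not give; the patients are selected as stable and ready for weaning, so deaths could be few.

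For ICU stay the cost is lost precision, of a size set by the unknown ratio k, together with the missing rule for deaths in the ICU. The affected outcomes are secondary; the primary sleep outcome is untouched. The change should be made, but it does not threaten the trial's main conclusion.

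**What to change.** Reword three rows of Table 1 before unmasking:

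- **Ventilator-free and antibiotic-free days:** days alive and free from randomisation to day 28 (and to day 8 for antibiotics), with patients who die within the window scored 0. State how days between ICU discharge and the end of the window are counted. Compare by a rank-based test and show mortality alongside.
- **ICU length of stay:** days from randomisation to ICU discharge, or at least adjust for the recorded pre-inclusion stay. Give deaths in the ICU the worst rank, or show survivors and non-survivors separately.

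The cost is small. Time zero is already randomisation, pre-inclusion stay is recorded and day-28 vital status is already an outcome, so the change is mainly one of wording. The downside is that a zero-for-death score is a composite: it mixes mortality with duration of treatment and must be read with its death component.
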